## Laboratory methods

### Surface immunophenotyping of peripheral blood mononuclear cells

Immunophenotyping will be used to characterise peripheral blood mononuclear cells (PBMC) isolated from blood samples of HIV-uninfected and HIV-infected ART initiators. PBMCs will be harvested by density centrifugation using Lymphoprep (Axis Shield, UK). PBMCs (2×10^6^) will be stained with anti-CD45 PerCP CY5.5, anti-CD3 AF700, anti-CD4 BV421, anti-CD8 PE Dazzle, anti-CD38 BV605, anti-HLA-DR APC CY7, anti-CD57 APC, anti-PD1 PE CY7, anti-CTLA4 PE and anti-CD223 FITC (all from eBioscience, UK) to determine the expression of these markers on the surface of T cells. In addition, 2×10^6^ PBMCs stained with anti-CD16 BV421, anti-CD14 PE, anti-HLA-DR PerCP CY5.5, anti-CD45 AF700, anti-CCR2 BV605, anti-CD11b APC, anti-CX3CR1 PE Dazzle and anti-CD38 FITC (all from eBioscience, UK) will be used for monocytes. Dead cells, CD3+ T cells and CD56+ Natural Killer cells will be excluded using LIVE/DEAD Fixable Aqua Dead Cell Stain (Thermo Fisher, UK), anti-CD3 BV503 and anti-CD56 BV503 (eBioscience, UK), respectively. Stained cells will be acquired on a BD LSRFortessa flow cytometer (Becton Dickinson, USA), and data will be analysed using FlowJo V.10.0 software (Tree Star, San Carlos, California). For each stained sample analysed, the median fluorescence intensity for each parameter will be normalised to its respective unstained control.

### Measurement of soluble markers of immune activation using multiplex bead array

A custom-made multiplex assay will be used to assess soluble markers of monocyte activation (CD163), systemic inflammation (IL-6) and endothelial activation (intracellular adhesion molecule 1) in plasma, isolated from blood samples of HIV-uninfected and HIV-infected ART initiators. Following isolation, plasma will be aliquoted and stored at −80°C until further use.

### Assessment of exposure to human CMV and VZV by ELISA

Quantitative VIDAS CMV IgG and IgM (bioMerieux, USA) and VZV glycoprotein IgG Low-Level Enzyme Immunoassay Kit (VaccZyme EIA) will be used to determine exposure to these viruses using a commercial ELISA platform. These kits will detect VZV antigen to a sensitivity and specificity of 97.8% and 96.8% and for CMV, 97.2% and 100% for IgG, and 100% and 97.4% for IgM, respectively.^34 35^ Plasma samples from HIV-uninfected and HIV-infected ART initiators stored at −80°C following collection will be used for these assessments.

### Human immunodeficiency virus

HIV infection will be diagnosed using two rapid tests in parallel (Determine HIV-1/2 (Abbott Laboratories, USA) and Uni-Gold HIV (Trinity Biotech, Ireland), and EIA rapid tests will be used as a tie-breaker. HIV-1 RNA levels in plasma will be measured using the Abbott RealTime HIV-1 assay with a lower limit of detection of 150 copies/mL (Abbott Molecular, Germany), according to the manufacturer’s instructions. CD4+ T cell count measurements will be performed using BD FACSCount machine (Partec platform).

### Procedures

Carotid-femoral PWV^36^ and CIMT^37^ measurements will be performed in accordance with expert consensus guidelines, using a standardised study protocol on the Vicorder system (SMART Medical, UK) and Philips CX50 machine (Philips Healthcare, UK), respectively. CIMT measurements will be performed by three trained operators. The intraclass correlation coefficient will be used to assess the performance of the operators against that of a certified neurosonologist prior to study commencement.

## Outcomes

### Primary outcomes

The primary outcomes are the progression of surrogate markers of CBD/CVD, namely PWV and CIMT, as well as the occurrence of new-onset vasculopathy defined by threshold values outlined in table 2.

### Secondary outcomes

The secondary outcomes are the following clinical events: (1) stroke, (2) MI, (3) unstable angina, (4) PVD, (5) all-cause death/vascular death and (6) immune reconstitution inflammatory syndrome (IRIS) vasculopathy (table 2). Changes in PWV or endothelial activation at 6 months post-ART initiation will be interpreted as a subclinical vascular IRIS event. These outcomes will be assessed through active surveillance in QECH inpatient wards for admissions of study participants. To improve capture of clinical outcomes, we will conduct brief telephone interviews with study participants about CBD/CVD symptoms and hospitalisations between study visits and facilitate unsolicited participant self-report. Clinical events and deaths in study participants will be reviewed by an independent endpoint review committee (ERC), comprising clinicians experienced in endpoint review. Each event will be reviewed and adjudicated by the ERC chair and two ERC reviewers, using a standard set of diagnostic criteria (table 2 and online supplementary S1). The format of reporting will be based on modifications of the INSIGHT network clinical diagnostic criteria. Deaths will be reviewed by the ERC using the International Classification of Diseases for causes of death classificaton.^23^ For death with limited clinical data, a validated verbal autopsy will be performed to ascertain the cause.^38^

10.1136/bmjopen-2018-025576.supp1Supplementary data

### Exposures

The exposure for primary objective 1 will be HIV status. Yearly HIV rapid tests in HIV-uninfected adults will be performed to exclude those with new HIV infections (figure 2).

**Figure 2 F2:**
[figure not shown]
Outline of study design for a 36-month cohort study. ART, antiretroviral therapy; cIMT, carotid intima-media thickness; PWV, pulse wave velocity; QECH, Queen Elizabeth Central Hospital.

Potential confounding and mediating factors will be recorded in study participants. This will include demographic factors, lifestyle and behavioural factors (eg, cigarette smoking and alcohol consumption), chronic comorbidities (ie, hypertension, diabetes), and cardiometabolic, renal and haematological factors (ie, full blood count, creatinine in urine and serum, body mass index, waist to hip ratio, random glucose, haemoglobin A1c, and lipid profile). Blood pressure will be measured at all study visits. Although vascular IRIS (table 2) will be considered as a primary endpoint, non-vascular IRIS will be defined as a risk factor. Where feasible, we will conduct PCR tests for common causes of IRIS in blood or cerebrospinal fluid samples. Adherence to ART and change of ART regimen will be assessed at all study visits through extraction of data from ‘ART master cards’; this is a government-supported monitoring tool used by all patients on ART in Malawi.

For objectives 2a–2c, markers of herpes and HIV viral antigenaemia and immune inflammation will be measured according to the outline in table 1. For primary objective 2a, reactivated latent herpes viral infections will be assessed by quantification of VZV and CMV antibodies. We will estimate the risk of atherosclerosis and arterial stiffening associated with current herpesviruses reactivation at baseline and sustained reactivation (ie, those that continue to have a high titre from measurement at baseline to 6 months after ART initiation). Hyperactivation of B cells may result in an expansion of polyclonal antibodies and thus an overestimation of virus-specific antibody titres. To address this issue and make appropriate adjustments for hypergammaglobulinaemia, we will (1) measure more than one herpesviruses and (2) measure total IgG.

For primary objective 2b, markers of immune activation, inflammation and endothelial activation will be measured (figure 1 and table 1). Quantitative cell surface immunophenotyping will be performed for CD4+ and CD8+ T cell activation (eg, Human Leukocyte Antigen – DR isotype [HLA-DR]) and senescence (eg, CD57) in a subset of participants. In all study participants, at baseline and at 6 and 12 months, we will measure soluble markers associated with systemic inflammation and endothelial activation.

For primary objective 2c, incomplete viral response and viral rebound of HIV will be measured by quantitative PCR in patients on ART.^39^ HIV viral load will be measured in patients on ART at 0, 6 and 12 months.

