**Figure 1 F1:**
[figure not shown]
Hypothetical pathway of the interplay between chronic viruses, immune activation, systemic inflammation, endothelial activation and vasculopathy. CIMT, carotid intima-media thickness; IL-6, interleukin-6; PWV, pulse wave velocity; VL, Viral Load; HLA-DR, Human Leukocyte Antigen-DR isotype; IFNγ, interferon gamma; TFNα, Tumour Necrosis Factor alpha; ICAM-1, intercellular adhesion molecules-1 and hsCRP, high-sensitivity C-reactive protein.

In addition to HIV, there is compelling evidence that reactivation of latent herpesviruses may be an important cause of vasculopathy. In HIV-uninfected elderly populations from high-income settings, latent cytomegalovirus (CMV) infection drives dysregulation of cell-mediated immunity,^15 27–29^ not dissimilar to what is described in HIV-associated immune activation.^29^ CMV and other viral proteins have been found in atherosclerotic plaques.^20^ Varicella zoster virus (VZV) can directly infect the vascular endothelium to cause vasculitis and subsequent stroke and was found to be the most common opportunistic infection (prevalence 15%) in a study of HIV-infected patients with stroke in Malawi.^12^ The seroprevalence of herpesviruses is high in SSA,^30^ particularly in HIV-infected populations.^16^

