### Study objectives

This study will test the hypothesis that immune activation and dysfunction, driven by HIV and reactivation of latent CMV/VZV herpesvirus infections, lead to increased CBD/CVD risk in adults aged ≥35 years in SSA. We will address this through the following objectives:

To determine if progression of the surrogate marker of CBD/CVD or occurrence of new-onset vasculopathy is higher in adults aged ≥35 years with HIV infection on ART compared with those without HIV.To determine if progression of surrogate markers of CBD/CVD or occurrence of new-onset vasculopathy is higher in adults aged ≥35 years with HIV/herpes viral antigenaemia or chronic immune activation compared with those without HIV/herpes viral antigenaemia or chronic immune activation. Specifically, we will determine if progression of surrogate markers or new-onset vasculopathy is higher in the following:In ART patients with reactivated latent herpes viral infection, compared with those without reactivated latent herpes viral infection.In ART patients with the highest 25% of markers for immune activation, inflammation or endothelial activation compared with the bottom 25%.In ART patients with incomplete virological suppression or virological resurgence of HIV, compared with those with suppressed HIV plasma viral load.

The secondary study objectives are to determine if viral antigenaemia or chronic immune activation increases the occurrence of the following clinical events: (1) stroke, (2) MI, (3) angina (excluding MI), (4) peripheral vascular disease (PVD), (5) all-cause death/vascular-related death and (6) immune reconstitution inflammatory vasculopathy.

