There will be three analysis time points: (1) after recruitment has finished and baseline data are available for all participants (baseline analysis); (2) once every participant has completed 6 months in the study (6-month analysis); and (3) at 36 months, when each participant has completed 24 months in the study (final analysis).

The baseline analysis will largely consist of descriptive statistics on participant characteristics and data recorded at baseline. Simple regression models will also be used to investigate relationships between exposure and outcome variables measured at baseline. Unadjusted analyses will consist of paired t-tests or Wilcoxon signed-rank tests (depending on whether the data are normally distributed or not) for continuously measured variables, and χ^2^ or Fisher’s exact tests (depending on contingency table cell counts) for binary and categorical variables. Adjusted analyses will be conducted using generalised linear models (GLMs).

The 6-month analysis will be limited in scope and serves two purposes: (1) characterise new-onset vasculopathy in HIV-infected participants who have initiated ART treatment at baseline (vascular IRIS) and (2) define vasculopathy outcomes for the final analysis. The main analysis of the study data will be conducted at the final analysis time point.

For objective 1 we will develop three regression models. Two GLMs will be developed to compare mean progression of arterial damage from baseline in HIV-infected ART patients and HIV-uninfected adults. These models will regress change from baseline PWV and CIMT, respectively, on HIV status. We will develop a third model to estimate the RR and population-attributable fraction of new-onset arterial damage in HIV-infected patients compared with HIV-uninfected adults.

For objective 2a, a set of GLMs will be developed to compare mean progression of vasculopathy in HIV-infected ART patients with and without reactivated latent herpes viral infection. These models will regress PWV and CIMT, respectively, on, on two log-transformed variables for antibody titres of CMV and VZV.

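### Objective 2a is worded as herpesvirus reactivation and antigenaemia, but the exposure measured is antibody level, so its conclusion should be limited to antibody level

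*Protocol article*

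**What the plan says.** **The question.** Under Study objectives, objective 2 compares adults "with HIV/herpes viral antigenaemia or chronic immune activation compared with those without HIV/herpes viral antigenaemia or chronic immune activation". Its part (a) asks about progression or new-onset vasculopathy "In ART patients with reactivated latent herpes viral infection, compared with those without reactivated latent herpes viral infection".

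**The measurement.** Under Exposures, "reactivated latent herpes viral infections will be assessed by quantification of VZV and CMV antibodies". Two exposures are derived: current reactivation at baseline, and sustained reactivation, meaning "those that continue to have a high titre from measurement at baseline to 6 months after ART initiation". No titre cut-off is given. The same paragraph warns that B-cell hyperactivation can inflate virus-specific titres, and it commits to measuring more than one herpesvirus and total IgG so that adjustment is possible.

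**The assays.** The laboratory section names a CMV IgG and IgM assay and a VZV IgG kit, which "will be used to determine exposure to these viruses using a commercial ELISA platform". It adds: "These kits will detect VZV antigen to a sensitivity and specificity of 97.8% and 96.8"%.

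**The schedule.** The herpesvirus block of Table 1 has two rows, CMV IgG and VZV IgG, each at baseline and 6 months. There is no row for CMV IgM, total IgG, or herpesvirus DNA or antigen. PCR is mentioned under Exposures only where feasible, for causes of IRIS.

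**The model.** For objective 2a, PWV and CIMT are regressed "on two log-transformed variables for antibody titres of CMV and VZV".

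**Background.** The Introduction states: "The seroprevalence of herpesviruses is high in SSA", particularly in HIV-infected populations.

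**The concern.** The exposure that is named (reactivation, antigenaemia) differs from the exposure that is measured (antibody level). By the protocol's own account the assays establish that a person has met the virus. Where past infection is common, a titre that stays high over six months is also what a stable past infection, or general B-cell activation in untreated HIV, could produce. The definition of sustained reactivation does not separate these.

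This affects the reading of either result. A positive association would be reported as an effect of reactivation, and the Introduction and Discussion link that finding to antiviral intervention. Yet it might partly reflect B-cell activation accompanying the inflammation that the study itself regards as a cause of vasculopathy. A null association would be read as evidence against reactivation when the proxy may simply have been weak.

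**Working it through.** **1. Named exposure against measured exposure**

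| Objective | Exposure as named | Exposure as measured | Direct? |
|---|---|---|---|
| 1 | HIV status | HIV rapid tests | Yes |
| 2a | Herpesvirus reactivation / antigenaemia | CMV and VZV antibody titre | No |
| 2b | Immune, inflammatory and endothelial markers | Those markers | Yes |
| 2c | HIV non-suppression or resurgence | HIV viral load by quantitative PCR | Yes |

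Only 2a relies on a proxy for the thing it names.

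**2. Internal disagreements on the 2a measurement**

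- CMV IgM is in the laboratory section but not in Table 1.
- Total IgG is promised under Exposures but is not in Table 1.
- The VZV kit is an IgG immunoassay, so it detects antibody; the laboratory section says antigen.

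**3. The plan's own figures, reproduced**

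Inputs from Sample size and statistical analysis: 800 HIV-infected; 18.4% excluded for abnormal baseline PWV; 20% lost; exposure prevalence 20%; RR 1.8; overall risk 18.4%; two-sided α = 0.05; 80% power.

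- Unexposed risk: 0.184 / (0.8 + 0.2 × 1.8) = 0.159. Exposed risk: 1.8 × 0.159 = 0.286. Both match the plan.
- Evaluable: 800 × 0.816 × 0.8 = 522, of whom about 104 are exposed.
- Needed for 28.6% v 15.9% at 1:4 (pooled variance, no continuity correction): 99 exposed, 495 in all. Inflated: 495 / 0.8 / 0.816 = 759, so 800 suffices. Power at 522 is 82%.

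The arithmetic is sound. It treats the 20% exposed as identified without error.

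**4. Illustration of an imperfect proxy**

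Assumptions, not in the documents: a high titre identifies true reactivation with sensitivity Se of 50–80% and specificity Sp of 70–90%, and the error is unrelated to outcome. With P = 0.20:

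- share labelled exposed: q = Se·P + (1 − Sp)(1 − P)
- truly exposed among those labelled exposed: A = Se·P / q
- truly exposed among those labelled unexposed: B = (1 − Se)·P / (1 − q)
- observed risks: 0.159 + 0.127·A and 0.159 + 0.127·B, where 0.127 = 0.286 − 0.159

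| Se / Sp | q | Risk, labelled exposed | Risk, labelled unexposed | Observed RR | Power at 522 |
|---|---|---|---|---|---|
| 1 / 1 | 0.20 | 0.286 | 0.159 | 1.80 | 82% |
| 0.8 / 0.9 | 0.24 | 0.244 | 0.166 | 1.47 | 50% |
| 0.8 / 0.8 | 0.32 | 0.223 | 0.166 | 1.34 | 34% |
| 0.7 / 0.9 | 0.22 | 0.240 | 0.169 | 1.42 | 42% |
| 0.5 / 0.8 | 0.26 | 0.208 | 0.176 | 1.18 | 13% |
| 0.5 / 0.7 | 0.34 | 0.196 | 0.178 | 1.10 | 8% |

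Worked case, 0.5 / 0.7: q = 0.10 + 0.24 = 0.34; A = 0.10 / 0.34 = 0.294; B = 0.10 / 0.66 = 0.152; risks 0.196 and 0.178; RR 1.10. The first and last imperfect rows are the extremes of the assumed range, so the observed RR runs from about 1.10 to 1.47.

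The calculation concerns a binary high/low titre and new-onset vasculopathy, as in the sample size section. It does not quantify the linear models on continuous log titre. If titre error is related to inflammation, bias could also run away from the null.

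**The case against.** The protocol does not hide that it uses a proxy. It says openly that antibody titre stands for reactivation, uses quantitative titre rather than serostatus (so high seroprevalence alone does not remove the contrast), recognises polyclonal inflation, and plans total IgG to deal with it. The article's model description lists no covariates even for objective 1, so the absence of total IgG there may only be condensation. All of this stands, and it limits the point to what titre may be called and to the disagreements between sections.

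Some stronger readings are tempting but not supported:

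- **That only IgG is measured.** This is true of Table 1 and of VZV. The laboratory section also names CMV IgM, so the two places disagree.
- **That the central hypothesis cannot be answered.** Only its herpesvirus part is affected, and even there a titre association can be estimated.
- **That most participants would be misclassified.** Under the assumed range the share is (1 − Se)·P + (1 − Sp)(1 − P), from 0.04 + 0.08 = 12% to 0.10 + 0.24 = 34%.
- **That IgM positivity or a rise in IgG should define reactivation.** The documents give no accuracy of any marker for reactivation, and a rise between baseline and 6 months could not classify the planned exposure of current reactivation at baseline.

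The objection leaves the mismatch between the objective's wording and the measured exposure in place.

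**Conclusion.** The point holds as one of construct and wording, confined to objective 2a. Antibody level is a serological proxy. On the protocol's own description of the assays, and its own caution about B-cell activation, a high or sustained titre does not by itself establish reactivation, and nothing scheduled as the 2a exposure measures herpesvirus antigenaemia. The sample size reproduces and is not in question.

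The size of any dilution is unknown. The observed RR of about 1.10–1.47 against a planned 1.8 rests on assumed sensitivity and specificity, error unrelated to outcome, and a binary exposure; it shows only that the effect of an imperfect proxy could be material. The text should be corrected before analysis, because the present wording would turn a titre association into a claim about reactivation with therapeutic implications.

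**What to change.** 1. **Restate the exposure and conclusion of 2a** as CMV/VZV antibody level, a serological proxy. Drop antigenaemia for herpesviruses in objective 2, and wherever the secondary objectives carry it over. In the laboratory section, correct VZV antigen to VZV antibody.
2. **Reconcile the laboratory section with Table 1**: schedule the CMV IgM assay already named at baseline and 6 months on stored plasma, and report it as a supporting marker, not as the definition of reactivation.
3. **Carry total IgG through**: add it to Table 1 and enter log total IgG in the objective 2a models for PWV and CIMT, as the adjustment promised under Exposures implies.

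The cost is some rewording, one covariate, and assays that the protocol already names or promises, with plasma already stored at −80°C. No change in sample size or visits is needed. The downside is a narrower claim: 2a would speak to antibody level and vasculopathy, not directly to reactivation.

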### Study participants

Study inclusion criteria will be (1) age ≥35 years and (2) resident of Blantyre. HIV-infected patients must further be (3) ART-naïve or initiated ART <10 days prior to enrolment and (4) initiating standard first-line ART. Adult controls must further be (5) HIV-uninfected. Study exclusion criteria are (6) clinical history of CBD/CVD, (7) pregnancy, (8) critical illness or symptomatic anaemia at baseline, and (9) enrolment in an intervention study. At the analysis stage abnormal pulse wave velocity (PWV) at baseline (as defined in table 2) will be excluded for new-onset vasculopathy analysis but not for progression of vasculopathy. The same approach will be applied for baseline carotid intima-media thickness (CIMT) measurements. If the study participant becomes pregnant after recruitment, they will be withdrawn.

**Table 2 T2:** Case definitions of primary and secondary endpoints for the study

Type	Definitions
Primary endpoint	Carotid intima-media thickness (CIMT)	*The occurrence of new-onset vasculopathy**(**CIMT, a measure of atherosclerosis**)*: CIMT >0.9 mm or >75th percentile of age/sex references values or presence of plaque on the carotid scan. *Progression*: total change in CIMT at 24 months from baseline.
	Pulse wave velocity (PWV)	*Occurrence of new-onset vasculopathy**(**PWV*,*a measure of arterial stiffness**)*: PWV >12 (m/s). *Progression*: total change in PWV at 24 months from baseline.
Secondary endpoint	Stroke	*Confirmed (**1**+**2**) or 3 or 4 or 5:* Acute onset with a clinically compatible course, including unequivocal objective findings of a localising neurological deficit. CT or MRI compatible with a diagnosis of stroke and current neurological signs and symptoms. Stroke diagnosed as the cause of death at autopsy. Clinical history and positive lumbar puncture compatible with subarachnoid haemorrhage. Death certificate or death note from medical record listing stroke as the cause of death.

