For objective 2b, we will again fit a set of GLMs, with change from baseline in PWV as response variable, this time to investigate if, in HIV-infected ART patients, there is an association between progression of vasculopathy and immune activation and inflammation biomarkers (IL-6, Intracellular adehesion molecule [ICAM], CD163). Specifically, for each marker, we will regress PWV on marker quantiles. After having built models for each marker, we will then develop comprehensive multiple regression models for PWV and CIMT with multiple independent markers as predictor variables.

For objective 2c, we will proceed as for objective 2a, but comparing HIV-infected ART patients with incomplete virological suppression or virological resurgence of HIV with those with suppressed HIV plasma viral load.

In addition to these analyses, given the repeated measurements for PWV, immune activation and inflammation markers, we will extend the GLMs for PWV to linear mixed models taking full account of the longitudinal nature of the data. Mixed models will also handle deviations from the visit schedule in a principled fashion and use all available data for dropouts. If a log link function is required for PWV in the GLMs, we will fit marginalised models using Generlaised Estimating Equations [GEE] instead of Linear Mixed Models [LMMs].

For the secondary study objectives, we will use univariate methods to assess the frequency of clinical events within exposure strata. If there are sufficient numbers of clinical events, we will develop Poisson or negative binomial regression models (depending on model fit) for each clinical event type to compare exposure-defined participants.

We will also use time-to-event models, specifically Cox proportional hazard models, to investigate associations between all-cause mortality and exposures.

As part of exploratory analyses, we will aim to identify risk groups that are potentially incompletely captured with the measured exposure variables. We will perform unsupervised group-based multitrajectory modelling of multivariate longitudinal patient trajectories to confirm any associations we have found using more traditional approaches.^44^

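### Resurgence is first visible at month 12, and sustained reactivation and incomplete suppression at month 6, but outcomes run from baseline with no landmark or time-updated exposure

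*Protocol article*

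**What the plan says.** **When exposure status becomes known.** The Exposures section of the protocol article plans two herpesvirus exposures for objective 2a. One is "current herpesviruses reactivation at baseline". The other, which needs a second sample, is "sustained reactivation (ie, those that continue to have a high titre from measurement at baseline to 6 months after ART initiation". For objective 2c it states: "HIV viral load will be measured in patients on ART at 0, 6 and 12 months". Under Sample size and statistical analysis, the 2c contrast is given as "incomplete virological suppression or virological resurgence of HIV with those with suppressed HIV plasma viral load".

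**When outcomes start.** Table 2 defines progression as "total change in PWV at 24 months from baseline" and "total change in CIMT at 24 months from baseline". For new onset, the Study participants section removes only those whose PWV (and, likewise, CIMT) was abnormal at baseline. Table 2 counts deaths after recruitment and defines vascular IRIS as new-onset vasculopathy within 6 months of starting ART.

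**How the two are linked.** The 2a GLMs use "two log-transformed variables for antibody titres of CMV and VZV", with no visit named. Objective 2c proceeds in the same way. Mortality is analysed with "Cox proportional hazard models, to investigate associations between all-cause mortality and exposures". The mixed-model extension is motivated by repeated PWV, immune activation and inflammation measurements; titres and viral load are not mentioned there. No landmark, delayed entry or time-updated exposure is named for any of these models.

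**The concern.** An exposure that is first observable part-way through follow-up is related to an outcome counted from the start. Two different problems can follow.

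First, if the exposure truly begins late, as resurgence does, the outcome includes vascular change that came before it. That change dilutes a real effect. It can also create a false one if early vascular disease, or something that goes with it, leads to later loss of viral control. Objective 2c is a primary objective, so this bears on a main result.

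Second, a label that needs a month-6 or month-12 sample can be given only to people who live to provide it. In a survival model counted from recruitment, the labelled group is then guaranteed survival up to that visit. If the comparator absorbs those who die earlier, the exposure looks protective. All-cause death is a secondary endpoint and its testing is exploratory, but the secondary objectives explicitly ask whether viral antigenaemia increases it.

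**Working it through.** **1. Timing, set side by side.** Patients enter ART-naïve or within 10 days of starting ART (Study participants), so the month-0 viral load cannot show response to treatment.

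| Exposure | First classifiable | Present earlier? |
|---|---|---|
| Reactivation at baseline (2a) | month 0 | aligned with the outcome |
| Sustained reactivation (2a) | month 6 | yes, the titre is already high at month 0 |
| Incomplete suppression (2c) | month 6 | generally yes, not yet suppressed at entry |
| Resurgence (2c) | month 12 (suppressed at 6, detectable at 12) | no, begins between months 6 and 12 |

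Vascular IRIS closes at month 6, so resurgence always follows it.

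**2. The plan's own figures.** With 18.4% overall risk, 20% exposed and RR 1.8, the unexposed risk is 0.184 / (0.8 + 0.2 × 1.8) = 0.159 and the exposed risk is 1.8 × 0.1586 = 0.286 (0.1586 being the unrounded unexposed risk). Both match the article. Evaluable HIV-infected participants number 800 × 0.816 × 0.80 = 522, or 418 unexposed and 104 exposed. The pooled-variance test of two proportions (two-sided 0.05) then has 82% power. The stated sample size reproduces and is not in question.

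**3. Vascular outcome, resurgence.** The share of the 24-month window before detection is 12/24 = 50%; if resurgence begins just after month 6 it is 6/24 = 25%. Assume risk accrues evenly and the exposure acts only from its onset:

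- Onset at month 12: exposed risk = 0.5 × 0.159 + 0.5 × 0.286 = 0.2225; RR = 0.2225/0.159 = 1.40.
- Onset at month 6: exposed risk = 0.25 × 0.159 + 0.75 × 0.286 = 0.254; RR = 1.60.

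If the whole 20% exposed group were resurgent, power would fall from 82% to 35% (month 12) or 61% (month 6). The 2c group also contains incomplete suppression, so these power figures are the extreme case.

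**4. Mortality.** Inputs are the article's 80 expected deaths (here all placed among the 800 patients, an assumption) and 20% exposure. The share *f* of deaths before classification is not given, so I take 25%, 40% and 50%. Assume no true effect and that early deaths are put in the comparator. Then exposed n = 0.2 × (800 − 80*f*) and exposed deaths = 0.2 × 80 × (1 − *f*); everyone else is comparator.

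| *f* | Exposed deaths/n | Comparator deaths/n | Null RR |
|---|---|---|---|
| 25% | 12 / 156 | 68 / 644 | 0.73 |
| 40% | 9.6 / 153.6 | 70.4 / 646.4 | 0.57 |
| 50% | 8 / 152 | 72 / 648 | 0.47 |

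If early deaths are excluded, or time starts at a landmark, both groups have the same risk and the ratio is 1.00. Simulated Cox fits (300 per scenario, 800 patients, month-6 cut) agree. Median HRs are 0.69, 0.51 and 0.43, with false rejection of 15%, 45% and 59%. With landmarks at month 6 or 12 they are 0.92–1.02, with rejection of 3–5%.

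**The case against.** **Early deaths.** A reader might infer that the plan puts early deaths in the wrong group. It does not say so. The 2c comparator is patients with suppressed viral load, and someone who dies before month 6 has no on-treatment viral load and fits neither side. Incomplete suppression seen at month 6 is already exposure before a death in months 6–12. Only a patient suppressed at month 6 who dies before month 12 could readily fall into the comparator for resurgence. For 2a, the Exposures text ties sustained reactivation to atherosclerosis and stiffening; the Cox sentence is general and gives no time origin or coding. This stands: the mortality figures are conditional illustrations, not a consequence of a stated rule.

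**Pre-exposure change.** A reader might also infer that a quarter of the PWV window precedes sustained reactivation. That is wrong, because the titre is high from baseline by definition. The same generally holds for incomplete suppression. In both, months 0–6 precede the label, not necessarily the exposure.

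**Survival and progression.** Anyone with a month-24 measurement in either group has lived past month 12, so observed progression carries no differential survival advantage. This stands, although the result still describes survivors.

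**Existing safeguards.** There is a separate 6-month analysis, and mixed models for PWV. The first describes early onset and helps define vasculopathy outcomes; it does not separate change before resurgence from change after it. The second could carry a time-varying viral load, but the text does not say it will.

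**Conclusion.** The point holds, most firmly for resurgence. The stated visit schedule and outcome definitions together place 25–50% of the PWV change window before resurgence begins, and up to half before it is detected. New-onset cases in that time are counted as if they followed it. Under even accrual and an effect starting at month 12, RR 1.8 becomes about 1.4; a different accrual pattern would change that figure, and reverse order could push the estimate the other way.

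For sustained reactivation and incomplete suppression the defect is narrower: results are conditional on surviving to month 6, and this is not stated. The baseline-titre analysis is correctly aligned.

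Bias towards protection in the Cox model is an open risk. It ranges from none (RR 1.00, early deaths excluded or a landmark used) to 0.73–0.47 (early deaths in the comparator, with assumed early shares of 25–50%). The plan should be changed on this point; the sample size is unaffected.

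**What to change.** 1. In the Cox and PWV mixed models, enter viral-load status as a time-updated exposure. Otherwise use a month-6 landmark for sustained reactivation and incomplete suppression and a month-12 landmark for resurgence. Report deaths before the landmark separately.
2. For resurgence, count PWV change and new onset from month 12. Table 1 already schedules PWV at months 6 and 12, so no new data are needed.
3. Keep the baseline-origin PWV analysis for baseline titres. Keep it also for sustained reactivation, described as applying to participants alive at month 6.
4. Do not relate resurgence to vascular IRIS, whose window closes before resurgence can be seen.
5. CIMT is scanned only at months 0 and 24 and cannot be re-based. Report CIMT against resurgence as association only.

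The cost is analysis wording plus some information. Landmark analyses lose events before the landmark, and for resurgence the first 12 months of the 24-month PWV window. Counting new onset from month 12 also leaves out patients who already crossed the PWV threshold, so that result applies to those still free of vasculopathy then. A time-updated exposure loses less and is preferable where the model allows it.
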